**Methods:**

The PTSC randomized controlled trial will evaluate the effectiveness of the PTSC Program on improved blood pressure control, healthcare utilization attributed to cardiovascular events, and healthcare costs. The study began in 2016 and will end in 2022. African American women who are 40–75 years old, have been diagnosed with hypertension, reside in Washington, D.C. or Baltimore, Maryland, and receive their care from Unity Health Care, a federally qualified health center in Washington, D.C., or Baltimore Medical System, a federally qualified health center in Baltimore, Maryland, are eligible to participate. Those randomized to the intervention group participate in the PTSC Program, which spans 13 weeks and comprises facilitator-led discussions, didactic training about hypertension management, and peer-based problem-solving concerning CVD risk factors and their amelioration. Blood pressure, weight, body mass index, waist circumference, self-reported adherence, physical activity, dietary practices, stress, and healthcare utilization data are collected at baseline, 13 weeks (end of the intervention), 9 months (months post-intervention), and 15 months (one year after the intervention). Healthcare costs will be computed at the end of the study. The study’s design is reported in the present manuscript, wherein we employed the SPIRIT checklist to guide its construction.

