### Baseline data collection

Upon consent, study participants complete a baseline survey composed of items measuring their health behaviors (including self-reported adherence, physical activity, and diet), psychosocial attributes (e.g., depressive symptomology, hypertension-related locus of control, and adaptive stress management techniques), perceived health status, and healthcare utilization.

Baseline measures of BP, waist circumference, height, and weight are also obtained. Blood pressure is assessed using a digital Omron 10 series device. Women are seated at rest for 5 min with their feet flat on the floor, and their arms raised at the heart level. Appropriate cuff sizes, based on each participant’s arm circumference, are attached to the device to detect their BP reading accurately.

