### Primary and secondary outcomes

The study’s primary outcomes are changes in blood pressure (baseline compared to 1-month post-intervention, 6 months post-intervention, and 1-year post-intervention); hospital utilization and admission, as well as emergency department utilization, attributable to cardiovascular events (obtained from Unity’s and BMSI’s medical records), and the intervention’s return on investment (which entails an interpolation of values from reported utilization from hospitalizations and ER, and lab and pharmacy visits, from Unity and BMSI). The secondary outcomes include changes in weight, BMI, and waist circumference; knowledge of causes and consequences of high blood pressure; hypertension-related locus of control; stress management techniques; self-reported physical activity, dietary behaviors, and blood pressure monitoring; and medication adherence. Data collection occurring at baseline, 13 weeks, 9 months, and 15 months post-intervention will capture blood pressure, weight, BMI, waist circumference, and the aforementioned secondary outcomes.

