### Analysis plan

Study data will be exported into Stata 15 for statistical analysis. We will set statistical significance at *p* ≤ 0.05. Baseline descriptive characteristics and outcomes will be analyzed using mean and standard deviation (SD) for continuous data, and counts and percentages for categorical data**.** We will conduct unequal variances t-tests in order to detect statistically significant differences between the treatment arms. To assess the impact of the PTSC program on participants’ blood pressure, weight, BMI, waist circumference, and all of the secondary outcomes, we will employ a difference-in-differences methodology to observe changes in participants’ outcomes at 3 months, 6 months, and 12 months post-intervention. We will also use multivariable regression analyses to discern whether or not participants’ outcomes improved as a result of receiving the PTSC intervention. Our models will control for patients’ sociodemographic characteristics (including age, marital status, and income), health insurance status, substance use (namely, smoking and drinking), and the presence of chronic conditions.

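### The regression left for the primary hospital and emergency utilization outcomes names no prior-utilization covariate, although utilization is collected at baseline: a cheap gain in precision of uncertain size is not taken

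*Protocol article*

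**What the plan says.** **Outcomes.** In Primary and secondary outcomes, the primary outcomes are change in blood pressure, "hospital utilization and admission, as well as emergency department utilization, attributable to cardiovascular events (obtained from Unity’s and BMSI’s medical records"), and the return on investment derived from utilization. The secondary list opens "The secondary outcomes include changes in weight, BMI, and waist circumference; knowledge of causes and consequences of high blood pressure" and goes on through psychosocial and behavioural measures. It contains no utilization item. The Hypotheses section predicts less cardiovascular hospital and emergency use in the intervention arm.

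**Analysis.** The Analysis plan states "To assess the impact of the PTSC program on participants’ blood pressure, weight, BMI, waist circumference, and all of the secondary outcomes, we will employ" difference-in-differences. It then adds multivariable regression for participants' outcomes in general. The covariates are sociodemographic characteristics, followed by "health insurance status, substance use (namely, smoking and drinking), and the presence of chronic conditions".

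**Baseline data.** The abstract's Methods paragraph lists "stress, and healthcare utilization data are collected at baseline, 13 weeks (end of the intervention), 9 months" and 15 months. Baseline data collection describes a survey whose contents end with "perceived health status, and healthcare utilization". Follow-up data collection says that administrative records track utilization and costs during the study period. It mentions no look-back before enrolment.

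**The concern.** Difference-in-differences brings the baseline value into the analysis of one primary outcome and of every secondary outcome. The other primary outcomes are analysed by a model for which no baseline value of utilization is named, although some form of it is in hand.

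Hospital and emergency counts are usually skewed, and a few frequent users can carry much of the variance. A woman's own prior use is the natural predictor of her later use. Without it, stable differences between women stay in the error term, apart from whatever the listed covariates absorb. Two things are at stake: the precision of the utilization and return-on-investment comparisons, and their sensitivity to a difference in prior use between the arms.

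**Working it through.** **1. Outcomes against methods.**

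| Outcome | Rank | In difference-in-differences list | Baseline value used |
|---|---|---|---|
| Blood pressure | primary | yes | yes |
| Weight, BMI, waist, other secondary outcomes | secondary | yes | yes |
| Cardiovascular hospital and emergency use | primary | no | none named |
| Return on investment | primary | no | none named |

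**2. The plan's own figure.** The only calculated figure is 308 women, for blood pressure control. With 80% against 65% and two-sided 0.05 it comes out closely. At 85% power, unpooled, n per arm = (0.80×0.20 + 0.65×0.35)×(1.960 + 1.036)²/0.15² = 155, or 310 in all. At 80% power with continuity correction the total is 302. The article states no power. It gives no event rate, effect size or ρ for utilization, so everything below rests on assumed values.

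**3. Variance of the arm contrast** (equal variances; follow-up only = 1). With baseline as a covariate the ratio is 1 − ρ². With difference-in-differences it is 2(1 − ρ). The last column is 440 × (1 − ρ²): the number of adjusted women to whom 440 unadjusted women are equivalent.

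| ρ (assumed) | Covariate | Difference-in-differences | 440 unadjusted are worth |
|---|---|---|---|
| 0.1 | 0.99 | 1.8 | 436 |
| 0.3 | 0.91 | 1.4 | 400 |
| 0.5 | 0.75 | 1.0 | 330 |
| 0.7 | 0.51 | 0.6 | 224 |

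Difference-in-differences improves on the follow-up-only contrast only when ρ exceeds 0.5. The covariate does not lose at any ρ.

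**4. Power.** Let d = 1.96 + z(unadjusted power). Adjusted power = Φ(d/√(1 − ρ²) − 1.96).
- From 80%, d = 2.802. At ρ = 0.3: 2.802/0.954 − 1.96 = 0.977, power 83.6%, gain 3.6 points. At 0.4 the gain is 6.4 points and at 0.5 it is 9.9.
- From 60%, d = 2.213. The gains are 4.1, 7.5 and 12.4 points.

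**5. Simulated counts.** Gamma-Poisson counts with a shared frailty (variance 1 or 2), 154 women per arm, assumed rate ratio 0.6, follow-up mean 1.25 times baseline, robust Poisson with and without log(1 + baseline count), 600 replicates per setting. Each cell gives power without and then with the covariate.

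| Assumed baseline mean | Frailty variance 1 | Frailty variance 2 |
|---|---|---|
| 0.05 | 13% → 14% | 9% → 10% |
| 0.1 | 27% → 26% | 29% → 29% |
| 0.2 | 47% → 48% | 40% → 44% |
| 0.5 | 73% → 78% | 61% → 75% |
| 1.0 | 87% → 95% | 72% → 94% |

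In the first three rows ρ is 0.05 to 0.30 and the gain is about 0 to 3 points; the one rounded gap of 4 is within simulation error of that. In the last two rows ρ is 0.32 to 0.64 and the gain is 5 to 22 points. A rerun with 1,500 replicates gave the same pattern. All of this is a best case, because the simulated baseline measures the same construct as the outcome without error.

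**6. Imbalance.** The share of a baseline difference left in the estimate is ρ with no adjustment, −(1 − ρ) with difference-in-differences, and 0 with the covariate. A difference of 0.2 SD in prior use leaves 0.06 SD unadjusted at ρ = 0.3 and 0.10 SD at ρ = 0.5. Difference-in-differences leaves −0.14 and −0.10 SD. With 216 and 125 women, the SD of a purely chance difference is √(1/216 + 1/125) = 0.112 SD.

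**7. Is more than chance possible?** Recruitment and randomization says attendees learn their arm before written consent is taken. If allocation was meant to be equal, as 220 per group implies, the split of 216 to 125 gives z = (216 − 125)/√341 = 4.9. That concerns the numbers enrolled. It says nothing about who the frequent users are.

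**The case against.** **This is a condensed article, and silence is not a decision.** Model family and cost methods are indeed commonly left to a fuller plan, and their absence is no finding. A reader might also infer that baseline utilization has been ruled out, but the article does not say so. What stands is narrower. The article does print a list of outcomes for the baseline-using method and a list of covariates, and prior utilization reaches these primary outcomes through neither.

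**The t-test.** A reader might infer that utilization will be tested by the unequal-variance t-test. That sentence follows the baseline descriptives and names no endpoint, so it may concern baseline only. The point does not need it.

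**Exclusion from difference-in-differences.** It is tempting to call this exclusion the defect. It is not: below ρ = 0.5 that method has the larger variance. The gap is the missing covariate.

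**The survey item is not the baseline of the outcome.** This stands. The outcome is cardiovascular use from medical records. The baseline item is a survey report of healthcare utilization with no stated recall window, cause or count format. The mismatch lowers ρ, but a covariate measured before the intervention remains usable.

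**The gain may be negligible.** This also stands. For rare events it is close to zero, and chronic conditions, already in the model, may absorb part of prior use.

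**Bias.** A reader might infer from 216 against 125 that the utilization estimate is biased. The documents do not show any difference in prior use between arms. Under intact randomization such a difference is noise, and only a fraction ρ of it carries over.

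**Conclusion.** The point holds as a cheap improvement of uncertain size. For the primary utilization outcomes, and the costs built on them, the stated regression omits a baseline variable that the trial collects.

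The direction is clear, since variance falls by about ρ². The size is not, because ρ, the event rates and the starting power are all assumed. The gain is about 0 to 3 points if events are rare (ρ up to about 0.3), rising to about 10 points at ρ = 0.5 from 80% power. It passes 5 points only from ρ of about 0.35 to 0.4. Protection against a prior-use imbalance is a second benefit. Such an imbalance could exceed chance here, because the arm is known before consent, but nothing in the article shows that it does.

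**What to change.** In the Analysis plan, state that cardiovascular hospital and emergency department counts are compared by randomized arm with a count model (negative binomial, or Poisson with robust standard errors), and that baseline utilization is added to the covariates already listed. Carry the same covariate into the cost comparison behind the return on investment. Do not simply add these outcomes to the difference-in-differences list.

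For the covariate, use the baseline survey item in whatever form it was collected: a count, for example as log(1 + visits), or a category. If the health centres can supply it, a look-back before enrolment in the same medical records would match the outcome better.

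The cost is a few lines of text and one covariate. With the survey item, no new participants, visits or staff are needed; a look-back would need one further records request. The downsides are small. A recalled, possibly any-cause item gives less than the figures above, and a simple rule is needed for missing baseline answers.

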### Study population and eligibility criteria

We plan to recruit up to 440 AA women receiving care at Unity Health Care (Unity), a Federally Qualified Health Center (FQHC) in Washington, D.C. and Baltimore Medical System Incorporated (BMSI), a FQHC with practices in Baltimore, Maryland. Eligible patient participants include English-speaking women who self-identify as AA, are 40 to 75 years old, have uncontrolled hypertension (previously defined as systolic blood pressure ≥ 140 mmHg or diastolic blood pressure ≥ 90) [2, 25], and receive their primary care at a Unity Health Care practice or a BMSI practice. Participants will be randomly assigned to receive the PTSC intervention or usual care at Unity or Baltimore Medical System Inc.

Thus far, we have recruited 341 participants into the study (PTSC intervention arm = 216; usual care arm = 125; see Fig. 1), all of whom receive care at Unity Health Care and live in metropolitan Washington D.C. In the next phase of the study, we will recruit an additional 100 AA women residing in Baltimore, Maryland and receiving care at a BMSI practice. Of note, hypertension diagnosis guidelines have changed since the study’s inception, and hypertension is now defined as systolic blood pressure ≥ 130 mmHg or diastolic blood pressure ≥ 80 [25]. However, we are maintaining the same blood pressure thresholds as we had at the start of the study in order to maintain equivalence in evaluating program impact between cohorts over time, given that the previous hypertension diagnosis criteria were central to the study’s eligibility criteria and recruitment process. Moreover, the patients are currently being managed to meet the prior guidelines. Our criteria reflect the current designation for Hypertension Stage 2 [25].

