### Power calculation

In order to detect a statistically significant difference in blood pressure control between the intervention and control groups post-exposure to the PTSC intervention, we need 440 participants (*n* = 220 per group) in our study. Our power calculations were based on the assumption of 80% HTN prevalence among study participants in both treatment arms at baseline, a two-sided alpha of 0.05, and a 15% reduction in the proportion of participants with high blood pressure after receipt of the PTSC intervention. The calculated sample size was 308, but our experience developing, implementing, and evaluating interventions with this target population suggests that we should anticipate a relatively high attrition rate. Thus, we computed a potential attrition rate of roughly 40%. In order to have sufficient power to detect a 15% reduction in HTN in the intervention group, we will recruit at least 40% above the estimated sample size, for a total sample size of 440 participants between Unity and BMSI health systems.

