## Discussion

Preliminary analyses of the baseline characteristics of the study’s participants reveal.

that, thus far, a substantial portion of participants assigned to the intervention group did not receive the intervention as intended. Of the 216 women randomly assigned to the PTSC intervention, 103 received the intervention as designed (that is, they attended at least 8 of the 13 Sister Circles), while the remaining 113 did not. This indicates a need for culturally- and economically-sensitive mitigation strategies that will encourage higher receipt of the intervention. In an effort to uncover some of the factors related to low exposure to the PTSC program, we created a short survey to elicit information about why they were not participating. Two of the top 3 reasons cited for non-involvement in the study were related to the accessibility of the Sister Circles (transportation and scheduling), and the other reason was a matter of personal health (not feeling well enough to attend). These realities attest to the difficulties associated with designing and implementing a randomized trial in the real-world context of engaging with a socioeconomically vulnerable study population, whose members may be grappling with multiple comorbid conditions and various structural determinants of health. Additional analyses indicate that most of the attrition observed thus far occurred between the recruitment meeting and participants’ first Sister Circle session, despite the fact that participants meet their facilitator at the recruitment meeting, and facilitators contacted study participants in between the recruitment session and the first Sister Circle session. Bearing in mind that the reduced number of study participants exposed to the intervention threatens our ability to detect statistically significant differences between the intervention and usual care groups, and to tackle the issue of attrition prior to the first Sister Circle, we have shortened the time between the recruitment meeting and the first Sister Circle session to less than two weeks. This information informs our approach for the third cohort of participants. We will make the Sister Circle schedules more flexible, provide transportation assistance, and create protocols for facilitators to follow up with participants prior to the start of their Sister Circle. In addition, we will allow study participants assigned to the intervention to choose their Sister Circle from a menu of Sister Circles that vary by time, i.e., from a daytime, evening, and weekend Sister Circle.

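### Blood pressure is to be analysed by difference-in-differences, with no baseline BP or cohort/site named as covariates; adjusting follow-up BP for both would be more precise and would guard against a possible link between site and arm

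*Protocol article*

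**What the plan says.** The Analysis plan names the method for blood pressure and the secondary outcomes: "we will employ a difference-in-differences methodology to observe changes in participants". It adds multivariable regression analyses, whose form is not given, and says the models will control for "sociodemographic characteristics (including age, marital status, and income), health insurance status, substance use (namely, smoking and drinking), and the presence of chronic conditions". Baseline BP, cohort and site are not named.

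The Power calculation describes a comparison of BP control between the arms after the intervention. It supposes that 80% of women in each arm have high BP at entry, tests two-sided at the 5% level, and states the effect as "a 15% reduction in the proportion of participants with high blood pressure after receipt of the PTSC intervention". This gives 308 women before attrition and 440 in total, 220 per group. No baseline-to-follow-up correlation is stated.

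Study population and eligibility criteria reports 341 women so far, 216 in the intervention arm and 125 in usual care, all from Washington, D.C. It continues: "we will recruit an additional 100 AA women residing in Baltimore, Maryland and receiving care at a BMSI practice". How the Baltimore women will be divided between arms is not stated. The Discussion describes changed delivery for the third cohort, including transport assistance and that "we will allow study participants assigned to the intervention to choose their Sister Circle from a menu of Sister Circles".

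**The concern.** Two features of the named analysis deserve attention.

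- **Precision.** Difference-in-differences subtracts the whole baseline value. When baseline and follow-up are imperfectly correlated, this adds noise that a fitted baseline coefficient would not. The Discussion already worries that low attendance threatens the ability to detect a difference, so avoidable imprecision matters here.
- **Site.** The trial moves to a second city and health system, in a later period and with changed delivery, after an unequal split in the first city. Differencing removes stable differences in BP level between sites. It does not remove differences between sites in how BP changes over time. If the arms end up with different shares of Baltimore women, such a difference enters the treatment estimate.

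**Working it through.** **Inputs from the article.** Two-sided alpha 0.05; 80% uncontrolled at baseline; a 15% reduction, read as absolute (80% to 65%); 308 women before attrition; 216:125 so far; 100 more from Baltimore.

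**Assumed.** Usual care stays at 80%; 80% power where a sample size is computed (the article gives no figure); rho from 0.2 to 0.7; equal baseline and follow-up variance for continuous BP.

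**Step 1: the plan's own figure.** The two-proportion formula is

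n per arm = [1.96·√(2·0.725·0.275) + 0.842·√(0.16 + 0.2275)]² / 0.15² = 138,

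or 151 with the continuity correction, so 302 in total. This is within 3% of 308. Without the correction, 85% power gives 316 (pooled) or 310 (unpooled). The relative reading (80% to 68%) gives 418 or more at 80% power and does not fit. A difference-in-differences formula would also pass through 308 for some rho between 0.3 (348) and 0.4 (298), so the number alone does not settle the method. The stated inputs do point to a plain post-intervention comparison: two proportions and alpha, with no correlation.

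**Step 2: continuous BP.** In units of the common variance per arm:

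- difference-in-differences: 2(1 − rho)
- post-intervention only: 1
- baseline-adjusted: 1 − rho²

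Adjusted over difference-in-differences is (1 − rho²)/[2(1 − rho)] = (1 + rho)/2. This is 0.65 at rho 0.3, 0.75 at 0.5 and 0.85 at 0.7. Difference-in-differences is worse than post-only when 2(1 − rho) > 1, that is, rho < 0.5.

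**Step 3: binary BP control.** The variances are 0.80·0.20 = 0.16 (baseline, and usual care at follow-up) and 0.65·0.35 = 0.2275 (intervention at follow-up). Summed over the arms:

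- difference-in-differences: 0.7075 − 2·rho·(0.16 + √(0.16·0.2275)) = 0.7075 − 0.7016·rho
- post-only: 0.3875
- baseline-adjusted: 0.3875·(1 − rho²)

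The first two are equal at rho = (0.7075 − 0.3875)/0.7016 = 0.46. Power is Φ(0.15/√(variance/154) − 1.96), with 154 per arm (308/2):

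| rho | Difference-in-differences | Post-only | Baseline-adjusted |
|---|---|---|---|
| 0.2 | 70% | 85% | 86% |
| 0.3 | 75% | 85% | 88% |
| 0.4 | 81% | 85% | 90% |
| 0.5 | 88% | 85% | 93% |
| 0.6 | 94% | 85% | 96% |

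If every woman is uncontrolled at baseline, the binary baseline variance is zero. Difference-in-differences and post-only then coincide, and adjusting for the binary baseline status adds nothing.

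**Step 4: site.** Bias = (Baltimore share in intervention − Baltimore share in usual care) × (Baltimore minus Washington difference in BP change). The split is not stated, so two are shown for illustration:

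| Baltimore split | Share, intervention | Share, usual care | Gap | Bias per 10 points of site difference in change |
|---|---|---|---|---|
| 63:37 (repeats 216:125) | 63/279 = 22.6% | 37/162 = 22.8% | about 0 | about 0 |
| 50:50 | 50/266 = 18.8% | 50/175 = 28.6% | 9.8 points | 1.0 point |

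For an assumed 5 mmHg site difference in BP change, the 50:50 split gives about 0.5 mmHg.

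**The case against.** The case on the other side has several parts.

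- **Difference-in-differences is a valid method, it uses baseline BP, and it matches a primary outcome defined as change.** True; it is less efficient, not wrong. But the match is no reason to prefer it. Once baseline is a linear covariate, the arm effect is the same whether the outcome is follow-up BP or change.
- **A condensed article may leave covariates to an analysis plan not shown.** This has force for the covariates, since the sociodemographic group is open-ended and nothing excludes site. It has none for the estimator, which is named.
- **Adjustment presumes comparable arms.** Under Recruitment and randomization, women learn their arm before giving written consent, and enrolment is unequal. If consent differed by arm, baseline BP could differ too, and the two methods would then rest on different assumptions. This stands, and is a reason to keep difference-in-differences as a sensitivity analysis.

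Two stronger readings are tempting. One is that the trial is underpowered because it was sized for one comparison and will be analysed by another. The documents do not support this: the loss depends on a rho they do not give, and above about 0.46 (binary) or 0.5 (continuous) difference-in-differences gains power. Eligibility also requires uncontrolled hypertension. If that holds at the baseline reading, there is no binary loss at all, although the assumed 80% prevalence sits uneasily with it.

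The other is that reaching 220 per group forces about 4 intervention and 95 usual-care women in Baltimore (220 − 216 and 220 − 125), nearly equating site with arm. That is arithmetic on the target, not a stated plan; no section gives the Baltimore split or says that randomisation ran by cohort.

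**Conclusion.** The point holds as an improvement available at no cost, not as an error that invalidates the plan.

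- **Precision.** Baseline adjustment beats the named method at any rho below 1 under the assumptions above. Variance is 15% to 35% lower for continuous BP at rho 0.7 to 0.3. For BP control at 80% baseline prevalence, power is 88% against 75% at rho 0.3 and 93% against 88% at rho 0.5. All of this rests on an assumed rho and on arms comparable at baseline.
- **Power against the sample-size comparison.** This is conditional, and no overall loss can be claimed.
- **Site.** The bias needs two things together: a Baltimore split other than about 63:37, and a site difference in BP change rather than in stable level. Neither is documented. The move to a new city, health system and delivery makes the second plausible enough to guard against.

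**What to change.** Reword the Analysis plan before follow-up outcomes are compared by arm:

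- Make the primary BP model a repeated-measures regression of follow-up BP on arm × visit, adjusted for baseline BP × visit and cohort/site × visit.
- For BP control, enter baseline BP as a continuous measurement. The adjustment then still works if nearly all women are above the threshold at entry. Report the effect as a difference in proportions, so that it stays on the scale of the Power calculation.
- Keep difference-in-differences as a sensitivity analysis. It also covers possible baseline imbalance from women learning their arm before consent.

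No particular Baltimore allocation is needed for this. An equal split would itself create the 9.8-point gap shown above, and the site terms handle whichever split is used. The cost is wording only: BP is measured at baseline and every follow-up, and each woman's cohort and site are known.
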